### Participant timeline

In the stepped-wedge design clusters, in this case floor units, cross over randomly (computer generated) from the control or standard of care condition to the intervention condition in a staggered fashion. The stepped wedge design will have 12 units allocated to a design matrix of 5 treatment wedges. Each wedge will last 75 days resulting in a study period of 12 months unless otherwise specified. The first step will be a baseline period in which no intervention is administered, where in the last step all clusters will be treated (Fig. 2). At the start of each wedge, there will be 2 weeks of burn-in to allow the clinical team to integrate the intervention with their workflow. Due to the pragmatic nature of the design, we are unable to blind providers to whether they were in the intervention unit or control unit. Patients will receive the same type of palliative medicine consult as they would normally receive in hospital, with the only difference being in how they were alerted. There was no additional data collected from patients and no follow up visits (i.e., all care will be done through the patient’s hospitalization).

**Fig. 2 Fig2:**
[figure not shown]
Stepped wedge design

### Data analysis plan

Summarized patient data will be characterized by age, sex, and baseline covariates entered into the machine learning algorithm (HCC diagnoses codes, previous utilization and lab measurements). All patients will be analyzed on an intention to treat status; this principle will be extended to the cluster status in the event of transfers between intervention and control units.

For all study outcomes, Bayesian estimation to account for design features in the stepped design will be used. Specially, time-to-event modeling to assess the effects of the intervention will be used to model time to palliative care and other time to event or count outcomes. The chosen model consists of a hierarchical regression treating the time-to-event as a heterogeneous Poisson process, allowing for adjustment to the event rate due to secular time effects and unit clustering. Our model is as follows: let Yijt indicate whether the ith eligible patient at the jth nursing unit during time t (t = 0,…,4) receives a palliative care consult during period t. Then, according to the stepped wedge designYijt ~ Poisson(λijt)log⁡(λijt) = μ + αj[i] + β1X[i] + δt[i] + 1*log(offset[i]) (1)where μ is the overall mean, and αj is a random effect for nursing unit (cluster) j, j=1, 2, …12, αj[i] ~ N(0,τ2). δt[i] is the multivariate autoregressive process of order 1, AR (1), with Gaussian noise to adjust for the secular trend, X[i] indicates the intervention at the jth clinical practice at time t. β1 capture the main effect for the intervention, and the offset is the patient’s time spent in the j nursing unit at time t (1). Statistical tests will be based on 95% credible intervals and effect estimates will be Incident rate ratios (IRR). For secondary binary outcomes, logistic regression will be used with the same design features. Stepped-wedge cluster randomization trials typically have more statistical power than other cluster randomized designs when clusters are correlated, because each cluster is able to serve as its own control. Because of the complex nature of the design, there was no suitable closed formed solution for sample size thus requiring the estimation of statistical power using Monte Carlo simulation [25]. Our model for the simulation consisted of the same hierarchical Poisson regression model (1). In Monte Carlo simulation, you design a model and repeatedly draw samples under a set of hypothetical sample sizes, treatment effects, and fixed nuisance parameters. Then, for each sample, you test your hypothesis and collect the number of positive results; this is your estimated power. To estimate reasonable parameters for the nursing unit mean and time trends for receiving palliative care consultation, we collected pilot data for all Mayo Rochester inpatient admissions in 2017 with palliative care consult status. With estimates of the nursing unit mean and secular trend, we have at least 80% power for the 12-month recruitment timeframe with 12 nursing units and an expected positive predictive value of 50% to detect incident rate ratios (IRRs) of 1.25 or greater. See Fig. 3 for the power curves; we tested various scenarios with varying number of nursing units and recruitment lengths. We choose the 12-month recruitment time frame and 12 nursing units because it was a good compromise between the power of the test (assuring we could detect a reasonable effect) and implementation (Palliative Medicine wanted to make sure they could set up a well-defined and accepted process on each of the selected intervention units to ensure intervention fidelity). Our final simulated dataset consisted of 2294 eligible encounters. The average cluster size was 143.4 encounters with a q1 and q3 of 49.5 and 200.5, respectively. The palliative care rate with no treatment was 18.4% with the highest cluster being 20.8% and the lowest cluster being 9.2%. There was a moderate to strong correlation in the day-to-day time effect of the AR(1) parameter (*r* = 0.67).

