### Data management

All data for all study outcomes, model covariates, and process measures will be collected through three principal means:
All input predictors and model predictions from the machine learning model are logged every time the algorithm is called and our stored in a study database.Study outcomes will be collected through electronically pulling administrative billing data or data from the health systems EHR.Process measures (number of Palliative Medicine accepts and reasons for rejection) will be collected through the daily logs transferred between the CTO and palliative care team.

For each variable pulled electronically, we will do a validation study to make sure that it is measuring the appropriate concept.

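### Model (1) lets units differ in level but not in trend; if unit consult rates vary by step beyond the shared trend, the 95% credible interval is too narrow and the power figure omits that variance

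*Protocol article*

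**What the plan says.** All of this is in the protocol article, under Methods/design.

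- **Purpose of the model** (Data analysis plan): a hierarchical Poisson regression "allowing for adjustment to the event rate due to secular time effects and unit clustering".
- **Unit term** (Data analysis plan): "αj is a random effect for nursing unit (cluster) j", normal with variance τ² and constant over time.
- **Time term**: "δt[i] is the multivariate autoregressive process of order 1, AR (1), with Gaussian noise to adjust for the secular trend". In the printed equation it carries a time subscript but no unit subscript.
- **Treatment and exposure**: "β1 capture the main effect for the intervention", and "the offset is the patient’s time spent in the j nursing unit at time t".
- **Power**: the Monte Carlo simulation is said to use this same model. It claims at least 80% power for an IRR of 1.25 with 12 units over 12 months.
- **Secondary binary outcomes**: logistic regression with the same design features.
- **Covariates**: "Summarized patient data will be characterized by age, sex, and baseline covariates entered into the machine learning algorithm". The stated use is description only; the linear predictor contains no patient covariate.
- **Score** (Data management): "All input predictors and model predictions from the machine learning model are logged every time the algorithm is called".

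**The concern.** A unit intercept plus a common time term says that, apart from treatment, every unit's log consult rate follows the same curve. The units are a mix of cardiology, critical care and oncology patients in two hospitals, followed through five periods of 75 days. Parallel movement is a strong assumption for such a mix. If one unit's case mix or referral practice shifts in one step and another's does not, model (1) has no term for that shift. The likelihood then treats every encounter in a unit-step cell as independent information about the rate, and the interval for the IRR understates the uncertainty. With few units crossing at each step, such shifts do not average out well. The power simulation sets the same variance to zero, so the power statement does not show its cost.

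A smaller matter is that the algorithm score is held for all patients in both conditions but is not used to reduce residual variation.

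**Working it through.** **Inputs from the article.** 12 units; 5 periods, the first all control and the last all treated; 2,294 encounters; untreated consult rate 18.4%, range over clusters 9.2% to 20.8%; 95% intervals; AR(1) correlation 0.67.

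**Assumptions.** Three units cross at each of four steps (Fig. 2 is not available). Between-unit SD τ = ln(20.8/9.2)/3.26 = 0.816/3.26 = 0.25, where 3.26 is the expected range of 12 standard normal values. The unit-by-step SD σ on the log rate is not in the article and is varied.

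**The plan's own figure.** The 80% power does not follow from the printed inputs. Events at the untreated rate: 2,294 × 0.184 = 422. Ignoring clustering and time, z = ln 1.25 × √422 / 2 = 0.2231 × 20.54 / 2 = 2.29, so power = Φ(2.29 − 1.96) = 63%. With half the encounters treated there are 1,147 × 0.184 + 1,147 × 0.23 = 475 events and power is 68%. A comparison of two proportions with 1,147 per arm gives 78%. Simulating the stepped wedge under model (1) gives 61% with no time effect and about 48% with a step-effect SD of 0.1.

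**Cell-level check.** Each of the 60 cells has 422/60 = 7.0 events, so the variance of a log rate is s² = 1/7.03 = 0.142. With I = 12, T = 5, U = 30 treated cells, W = 270 (squared column totals) and V = 90 (squared row totals), the model's own variance of log IRR is

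I·s²(s² + Tτ²) / [(IU − W)s² + (U² + ITU − TW − IV)τ²]
= 12 × 0.142 × (0.142 + 0.3125) / (90 × 0.142 + 270 × 0.0625)
= 0.776 / 29.67 = 0.0261, so SE = 0.162.

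The true SE of the same estimator, when σ² is present but unmodelled, is the sandwich variance with σ² added to each cell. The false-positive rate is 2Φ(−1.96 × 0.162 / true SE).

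**Simulation check.** 2,000 runs per scenario, unequal unit sizes, binary outcome, step-effect SD 0.1 with AR(1) correlation 0.67, Poisson likelihood, variances treated as known. False-positive rates under no effect:

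| σ | Cell-level true SE (ratio to 0.162) | Cell-level rate | Simulation, independent deviations | Simulation, autocorrelated within unit | Simulation, independent deviations, term added |
|---|---|---|---|---|---|
| 0 | 0.162 (1.00) | 5% | 3% | – | – |
| 0.1 | 0.167 (1.03) | 6% | 4% | – | 3% |
| 0.2 | 0.181 (1.12) | 8% | 9% | 6% | 4% |
| 0.3 | 0.202 (1.25) | 12% | 13% | 11% | 3% |
| 0.4 | 0.228 (1.41) | 16–17% | 21% | 14% | 4–5% |

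In the simulation with independent deviations, model (1) reports an SE of 0.125, while the actual SD of log IRR is 0.141 / 0.162 / 0.195 at σ = 0.2 / 0.3 / 0.4. Mean bias over all scenarios lies between −0.011 and +0.005.

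**Sensitivity.** At σ = 0.3 the rate is 17% with no step effect and 12% with a step-effect SD of 0.5. The printed average cluster size of 143.4 implies 2,294/143.4 = 16 clusters, not 12. With 12 × 143.4 = 1,721 encounters, the rates at σ = 0.1 / 0.2 / 0.3 are 4% / 6% / 10%.

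**Scale of σ.** With τ = 0.25, the correlation of a unit's true log rate between two steps is 0.0625/(0.0625 + σ²), which is 0.86 / 0.61 / 0.41 / 0.28 for σ = 0.1 / 0.2 / 0.3 / 0.4. The upper values imply that the units' order changes a good deal from step to step.

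**Score adjustment.** Patient-level simulation, 600 runs, assumed score effect of 0.4 and 0.7 on the log rate per score SD. The SD of log IRR falls from 0.159 to 0.154 (3%) and from 0.152 to 0.143 (6%). If unit case mix also drifts by 0.3 score SD between steps, it falls from 0.170 to 0.155 (9%) and from 0.179 to 0.150 (16%). Each SD has a relative Monte Carlo error of about 1/√1,200 = 3%, so the no-drift gain is small and only roughly measured.

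**The case against.** Four points can be made for the plan.

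1. **The AR(1) term is called multivariate.** A single shared series would not normally be described so, and unit-specific series are a possible reading. The printed subscript does not show this. The equation also indexes time as 0 to 4 while the reported correlation is between days. The text is therefore ambiguous, and clarification comes first.

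2. **There is no bias.** A reader might infer that drift within a unit is systematically read as intervention effect. The article does not support that: crossover order is random and computer generated, common drift is taken up by the time term, and simulated bias is about zero. Drift near a crossover can mislead in the one trial realised, but that is variance. Systematic bias would need drift linked to the time of crossover, and nothing in the article shows it.

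3. **The harm depends on an unstated SD.** This stands. A Poisson likelihood on a binary outcome is somewhat conservative, and for binary data it absorbs independent deviations up to about σ = 0.15. That protection is accidental, however, and is exhausted at larger values.

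4. **Covariate adjustment is optional.** An unadjusted primary analysis of a randomised comparison is not an error, and further covariates may be left to an analysis plan that is not shown. The score is therefore a suggestion for precision only. Service line would not help: to the extent that it is fixed for a unit, the unit intercept already absorbs it, and it cannot address drift within the unit.

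**Conclusion.** As printed, the primary model and the power simulation both assume zero unit-by-step variance. If that variance is real, the 95% credible interval is too narrow. With independent deviations, the false-positive rate is about 4–6% at an SD of 0.1, 8–9% at 0.2, 12–13% at 0.3 and 17–21% at 0.4. It is lower at 0.2 and above if the drift is autocorrelated within unit, or if there are 1,721 encounters rather than 2,294. These figures assume τ of 0.25, three units crossing per step and equal exposure per encounter. The simulation also uses known variances and normal intervals in place of a full Bayesian fit.

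The conclusion is conditional on the AR(1) being one shared series; if it is unit-specific, most of the point falls away. It would also go too far to call the 80% power wrong. The secular SD, the exposure times, the role of the 50% predictive value and Fig. 3 are not available, so the figure is only not reproducible from what is printed. The change should be made before analysis; the point does not invalidate the design.

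**What to change.** 1. State whether the AR(1) process is shared or unit-specific, and whether its time index is the step or the day.
2. If it is shared, add a unit-by-step random effect (or a unit-specific AR(1)) to model (1) and to the logistic models for secondary outcomes. Give its SD a stated weakly informative prior, for example half-normal with the scale written down, and repeat the analysis with the scale halved and doubled.
3. Rerun the power simulation with this term over a range of its SD, such as 0.1 to 0.4, and report the result.
4. Add the algorithm score at first eligibility, fixed before any intervention contact, as a prespecified covariate. The algorithm runs on all inpatients, so the score exists in both conditions.

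**Cost.** No new data, only analysis wording and a rerun. The interval widens to the extent that the variance is real: in the simulation the reported SE goes from 0.125 to 0.130 / 0.142 / 0.158 / 0.177 at σ = 0.1 / 0.2 / 0.3 / 0.4. Power at IRR 1.25 goes from about 48% to 43% / 35% / 31% / 25% under the same assumptions. The estimate itself becomes no less precise: its actual SD is 0.138 / 0.152 / 0.174 at σ = 0.2 / 0.3 / 0.4, against 0.141 / 0.162 / 0.195 without the term. With about 7 events per cell the new variance is weakly identified, which is why the prior needs to be stated and tested.

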### Aims of the study

The objective of this study is to evaluate whether the Control Tower solution accurately identifies patients who may benefit from a comprehensive review by a palliative care specialist and decreases time to receiving a palliative care consult in hospital. By creating an algorithm that automatically screens and monitors patient health status during their hospitalization, the hypothesis being tested is that patients will receive *needed* palliative care earlier than under the usual course of care.

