### Eligibility criteria

The recruitment and enrollment is broad and is designed to mimic the actual use of the Control Tower in practice. To be included in the trial, patients will need to be admitted to either inpatient facility during the study period. Patients will need to have a risk score of at least 7 (out of 100) from the algorithm. Patients will be excluded from review if they under the age of 18, previously seen by palliative care during the current hospital encounter, currently enrolled in hospice, or currently followed by a palliative care team. In addition, patients with an expected discharge in the next 24 h and patients who do not provide research authorization to review their medical records for general research studies in accordance with Minnesota Statute 144.335 will be excluded from the study.

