### Outcomes

For all study outcomes, data will be collected through either the electronic medical record or administrative billing system at trial completion and unless otherwise noted each outcome will be determined during the patient’s inpatient stay. The primary outcome will be time to palliative care as measured by the electronic record of a consult by Palliative Medicine. Data will go through quality checking quarterly, at each step during the burn-in period, and before finalization.

The secondary outcomes are as follows:
The number of inpatient palliative care consults—measured by the number of palliative care consults in the inpatient units of interest.Time to palliative care per unit—measured as time in hours from alert to the electronic record of consult by the palliative care team in the inpatient setting for each of the 12 nursing units.Transition time to hospice-designated bed—for all patients with Medicare insurance the time from alert until transferred to a hospice-designated bed for an inpatient encounter.Time to hospice designation—measured as time in hours from alert to the electronic record of consult by the hospice care team for an inpatient encounter.Emergency Department visit within 30 days of discharge—measured by the number of study participants who upon discharge from the inpatient setting are readmitted to the Emergency Department at any Mayo Clinic facility within 30 days (excluding inpatient readmissions through the Emergency Department).Hospitalization or readmission within 30 days of discharge—measured by the number of study participants who upon discharge from the inpatient setting are readmitted to an inpatient unit at any Mayo Clinic facility within 30 days (excluding transfers and planned readmits).ICU transfers—measured by the number of study participants who transferred to an ICU during their inpatient stay.Ratio of inpatient hospice death to non-hospice hospital deaths—measured by the number of deaths of study participants in hospice designated beds by the number of deaths in non-hospice beds.Rate of discharge to external hospice—measured by the number of participants whose electronic health record indicates discharge to external hospice.Inpatient length of stay—measured as time from admission to discharge from hospital for all study participants.

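### Read literally, the primary Poisson model divides a yes/no consult indicator by time in the unit, so it estimates consults per unit of stay and not a time-to-consult rate ratio

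*Protocol article*

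**What the plan says.** The Aims of the study section hypothesises that patients receive needed "palliative care earlier than under the usual course of care". The Outcomes section states: "The primary outcome will be time to palliative care as measured by the electronic record of a consult by Palliative Medicine". That sentence gives no time origin. The per-unit secondary version does give one: it is "measured as time in hours from alert to the electronic record of consult by the palliative care team". The two secondary hospice-timing outcomes also start at the alert.

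The Data analysis plan describes the primary model as "treating the time-to-event as a heterogeneous Poisson process". It then defines the terms of model (1):

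- The response Y records whether an eligible patient "receives a palliative care consult during period t".
- The offset is the log of the patient's "time spent in the j nursing unit at time t".

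Eligibility requires a score of at least 7. It excludes, among others, patients "previously seen by palliative care during the current hospital encounter". Inpatient length of stay is a secondary outcome. The power simulation is said to have used the same model (1).

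**The concern.** A Poisson regression with a log-exposure offset is equivalent to a time-to-event model only when each patient's exposure ends at the event. With a 0/1 response and an offset of time in the unit, a consult on day 1 of a 10-day stay contributes the same as one on day 9. The model then compares consults per unit of stay.

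The start of the clock has the same problem. A patient enters only on reaching a score of 7 with no earlier consult in the encounter, so any unit time before that point is event-free by construction. The stated offset does not exclude it.

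At stake is whether the incidence rate ratio measures what the trial set out to change. The denominator may also respond to the intervention, because length of stay is itself an outcome.

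**Working it through.** **Inputs from the article.** Control consult proportion 18.4%, target ratio 1.25, 2294 simulated encounters, 12 units, 5 periods. **Assumptions.** The article gives no stay or consult-time distribution, so every stay length below is assumed.

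**The plan's own figure.** The stated power of at least 80% could not be reproduced: the unit variance, the AR(1) noise variance, the stay distribution and the way the 50% positive predictive value enters are not given. It does not decide this point.

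**1. True consult-rate ratio 1.25, stay unaffected, offset = full time in the unit.**
- Fixed stays: cumulative hazard = −ln(1 − 0.184) = 0.2033. Treated proportion = 1 − exp(−1.25 × 0.2033) = 0.2244. Ratio = 0.2244/0.184 = **1.22**.
- Exponential stays: control consult-to-discharge hazard ratio = 0.184/0.816 = 0.2255. Treated proportion = (1.25 × 0.2255)/(1 + 1.25 × 0.2255) = 0.2199. Ratio = 0.2199/0.184 = **1.195**.
- With exposure stopped at the consult, the exponential case returns 1.25. A stepped-wedge simulation (400 runs, exponential stays, three units per step assumed, fixed unit effects, no AR(1) term) gave 1.25 with the at-risk offset and 1.19 with time in the unit. Rejection rates in that simplified setting fell from 58% to 37% without period effects and from 27% to 14% with them.

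**2. Pure timing shift: same proportion consulted, same stay.**
- Time-in-unit offset: numerator and denominator are both unchanged, so the ratio is exactly **1.00**, whatever the stay.
- At-risk offset, constant rate, 8-day stay, consult moved from day 5 to day 2.5: mean exposure is 0.184 × 5 + 0.816 × 8 = 7.448 against 0.184 × 2.5 + 0.816 × 8 = 6.988. Ratio = 7.448/6.988 = **1.07**.
- At-risk, flexible baseline, same example: let θ be the hazard ratio. All treated events fall at day 2.5 (equal risk sets) and all control events at day 5 (treated risk set reduced to 0.816). The score equation is 1/(θ + 1) = 0.816θ/(0.816θ + 1), so θ² = 1/0.816 and θ = **1.107**.

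**3. Precision.** For a 0/1 outcome with fixed exposure, the variance of the log proportion is (1 − p)/(np), but the Poisson model uses 1/(np). The standard error is inflated by √(1/0.816) = **1.107**. Simulated binary data (2294 encounters, 600 runs) gave a mean model standard error of 0.177 against an empirical SD of 0.159, a ratio of 1.11.

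**4. Dependence on length of stay, no effect on consulting.**
- Proportion consulted unchanged, mean stay 5% or 10% shorter: 1/0.95 = **1.05**, 1/0.90 = **1.11**.
- All stays 20% shorter, consult hazard unchanged, exponential stays: proportion = 0.2255/(0.2255 + 1.25) = 0.1528. Ratio = (0.1528/0.8)/0.184 = **1.04**, because fewer patients are consulted.
- Stay after the consult halved, exponential stays: mean stay falls by the factor 1 − 0.5 × 0.184 = 0.908, so the ratio is 1/0.908 = **1.10**. Simulation gave 1.115 to 1.125, with the at-risk ratio at 1.006 to 1.017 in the same runs.

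**The case against.** The strongest reply is that time at risk was intended. The section announces time-to-event modelling by a Poisson process and defines Y for eligible patients, and a patient already seen by palliative care is no longer eligible. On that reading exposure starts at eligibility and ends at the consult, the model is the ordinary exponential likelihood, and the variance problem disappears. This reading is possible. A reader might infer that the plan expressly keeps time after the consult and starts at unit entry; it says neither. But the article prints the equation and defines each term, and the offset as defined carries no start or stop. That is a stated definition that gives the wrong quantity if coded as it stands, and not detail left to an analysis plan.

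Three further objections stand:

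- A reader might infer that any 5 to 10% reduction in stay raises the ratio to 1.05 to 1.11. That holds only if the proportion consulted is unchanged. If only stay after the consult shortens, and consulted and other patients have equal mean stays, a 10% fall in overall mean stay needs consulted patients' stay to fall by about 54% (0.10/0.184).
- The attenuation to 1.20 to 1.22 and the wider intervals both work against a false positive.
- A reader might expect a corrected offset to capture earlier consults fully. It does not: the pure-shift example reaches only 1.07 to 1.11, still below the 1.25 used for power. Weak sensitivity to timing alone belongs to any rate or hazard ratio at this event proportion.

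**Conclusion.** The point holds for the model as printed. Its ratio is consults per unit of time in the unit, while the hypothesis and primary outcome concern time to consult.

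The exact 1.00 under a pure timing shift needs no assumed stay length. The shrinkage of 1.25 to 1.20–1.22 rests on the 18.4% consult rate, a constant consult hazard, and fixed or exponential stays unaffected by the intervention. The 11% excess width rests on a 0/1 outcome with fixed exposure. The upward bias from shorter stays is real in mechanism, but its size is conditional and cannot be fixed from the article, which gives no stay data. The effect of counting time before the alert was not quantified.

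The documents do not support saying that the primary result is bound to be misleading, or that the investigators certainly meant to count time after the consult.

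**What to change.** Redefine the offset in model (1) as time at risk. Exposure runs from the first qualifying alert (first score of at least 7 while otherwise eligible) to the earliest of consult, discharge, death or end of period, with Y = 1 only in the interval containing the consult. State the same origin in the primary outcome sentence, which brings it into line with the secondary outcomes that start at the alert. Preferably split each encounter by day since alert and include a piecewise baseline rate, so that the same hierarchical Poisson code fits a piecewise-exponential model.

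Add a sentence saying that the resulting ratio remains only weakly sensitive to a pure timing shift, about 1.07 to 1.11 in the 8-day example. Because the power simulation used model (1), confirm which exposure it used.

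The cost is wording and a data-reshaping step. The algorithm runs on all inpatients and its predictions are logged at each call, so alert times can be derived in both arms, and consults come from the electronic record.

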**Methods:**

To that aim, we will conduct a two-armed stepped-wedge cluster randomized trial rolled out to two inpatient hospitals to evaluate whether a machine learning algorithm accurately identifies patients who may benefit from a comprehensive review by a palliative care specialist and decreases time to receiving a palliative care consult in hospital. This is a single-center study which will be conducted from August 2019 to November 2020 at Saint Mary’s Hospital & Methodist Hospital both within Mayo Clinic Rochester in Minnesota. Clusters will be nursing units which will be chosen to be a mix of complex patients from Cardiology, Critical Care, and Oncology and had previously established relationships with palliative medicine. The stepped wedge design will have 12 units allocated to a design matrix of 5 treatment wedges. Each wedge will last 75 days resulting in a study period of 12 months of recruitment unless otherwise specified. Data will be analyzed with Bayesian hierarchical models with credible intervals denoting statistical significance.

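### The simulated dataset reported beside the power claim (2294 encounters, mean cluster size 143.4) implies 16 clusters, so the two figures cannot both describe the 12-unit trial

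*Protocol article*

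**What the plan says.** The number of clusters is fixed at 12. The Abstract defines the cluster: "Clusters will be nursing units which will be chosen to be a mix of complex patients from Cardiology, Critical Care, and Oncology". Participant timeline gives the count: "The stepped wedge design will have 12 units allocated to a design matrix of 5 treatment wedges". In the Data analysis plan section, the unit index of the analysis model runs from 1 to 12, and the same model is said to have generated the simulations.

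That section states the power claim for 12 units: "we have at least 80% power for the 12-month recruitment timeframe with 12 nursing units and an expected positive predictive value of 50" per cent, "to detect incident rate ratios (IRRs) of 1.25 or greater". It adds that other designs were explored ("we tested various scenarios with varying number of nursing units and recruitment lengths") and explains why 12 units over 12 months was chosen. The dataset description follows directly: "Our final simulated dataset consisted of 2294 eligible encounters", and "The average cluster size was 143.4 encounters with a q1 and q3 of 49.5 and 200.5, respectively". It also gives a consult rate without treatment of 18.4%, with unit rates from 9.2% to 20.8%. No cluster count is given for this dataset.

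**The concern.** A reader who has just been told that 12 units were chosen will take the dataset described next as the 12-unit run. Its total and mean do not agree with 12 units.

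These sentences are the article's only statement of how many eligible encounters are expected and how they spread over units. Cluster count and total size are main drivers of power in a stepped-wedge trial. If the description belongs to a different set of units, the quartiles and unit consult rates also fail to describe the trial, and nobody can tell from the article what sample size the power claim rests on.

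**Working it through.** **Inputs**, all from the Data analysis plan section unless noted:
- total encounters N = 2294
- mean cluster size m = 143.4
- clusters in the trial K = 12 (also in the Abstract and Participant timeline)

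**Step 1. Try to reproduce the stated mean with 12 clusters.** Mean = N/K = 2294/12 = 191.2. The stated mean is 143.4, so it is not reproduced.

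**Step 2. Find the number of clusters the two figures imply.** N/m = 2294/143.4 = 15.997. The mean is rounded to one decimal, so it lies between 143.35 and 143.45. The implied count is then between 2294/143.45 = 15.99 and 2294/143.35 = 16.00. For whole numbers near this:

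| Clusters | 2294 / clusters |
|---|---|
| 12 | 191.2 |
| 15 | 152.9 |
| 16 | 143.375, rounds to 143.4 |
| 17 | 134.9 |

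Only 16 fits.

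**Step 3. Size of the discrepancy if there are 12 units.**
- If the mean is right: total = 12 × 143.4 = 1720.8, about 1721. The shortfall against 2294 is 573, and 573/2294 = 25%.
- If the total is right: mean = 191.2 instead of 143.4.

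**Step 4. Look for a reading that rescues 12 units.**
- *The cluster means a unit-by-period cell.* 2294/(12 × 5) = 38.2, and 2294/(12 × 4) = 47.8. Neither is 143.4.
- *The mean excludes burn-in time.* Participant timeline gives two weeks of burn-in per 75-day wedge. With even accrual (an assumption), 2294 × 61/75 = 1866 encounters remain, or 155.5 per unit. If the baseline wedge loses nothing, the kept share is (75 + 4 × 61)/375 = 319/375, which gives 1951 encounters, or about 163 per unit. Neither is 143.4.
- *Transferred patients count in more than one unit.* This would push a 12-unit mean above 191.2, away from 143.4.
- *Rounding.* It cannot explain a 25% gap.

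The quartiles (49.5 and 200.5) and the range of unit rates are compatible with either 12 or 16 clusters, so they do not settle the matter.

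**The case against.** The strongest reply is that this is an inconsistency in a description, and that the power claim is untouched. The article ties that claim explicitly to 12 units and 12 months, and says that several unit counts were simulated. If the two descriptive sentences summarise a 16-unit scenario, the 12-unit power may still have been read correctly off the power curves. If only the mean was mistyped, the 2294 encounters behind the power do not change. The 12-unit design itself is consistent throughout, and neither the analysis model nor the treatment effect being estimated is affected.

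Most of this stands. A reader might infer that the dataset behind the power claim really had 16 clusters, and hence that the stated power does not apply to this trial. The article does not support that. It gives no cluster count for the dataset, and a misreported total or mean would produce the same ratio. The link between this dataset and the power claim rests only on its being called final and on the order of the sentences.

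A reader might also want to turn the 25% shortfall into a loss of power. That cannot be done from the article: the between-unit variance, the offsets and the way the 50% positive predictive value entered the simulation are not given. Any figure would rest on a simplified formula and assumed inputs.

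The reply does not remove the contradiction, which lies in two adjacent sentences of running text and needs no assumption.

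**Conclusion.** The point holds as a contradiction in the reported sample-size figures. A total of 2294 with a mean of 143.4 means 16 clusters; the trial has 12. One of three things is true:
- both figures come from a different scenario;
- the total is wrong, with 1721 the 12-unit value (25% lower);
- the mean is wrong, with 191.2 the 12-unit value.

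The article does not show which. The conclusion rests only on the two stated figures, the stated number of units, and the ordinary meaning of an average. Whether the claim of at least 80% power is affected remains open: it may be correct, but the dataset printed next to it cannot be used to support it as it stands.

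**What to change.** 1. Check the existing simulation output and state how many clusters the reported dataset contains.
2. Replace the total, mean, quartiles and unit consult rates with those of the 12-unit, 12-month run. If that run had 2294 encounters, the mean becomes 191.2 and the quartiles need re-checking. If its mean was 143.4, the total becomes about 1721.
3. Confirm that the statement of at least 80% power at an incidence rate ratio of 1.25 comes from that 12-unit run. If it does not, restate the power from that run.

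The cost is small: re-reading saved output, or at most re-running one scenario, and correcting a few sentences. The design and the analysis model do not change.
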